### Recruitment and randomization

We are implementing two recruitment methods. For 12 purposively selected practices (from those who consent), researchers visit each practice monthly and allocate participants to each trial arm by using a pregenerated randomization list (in-practice method). Each month, the trial statistician draws up the randomization lists stratified by general practice. As all patients within a practice are assigned at one time, and to minimize the imbalance in participants between arms, random allocation uses blocks of three. The preordered randomization list is matched by the researchers to the existing order of the clean eligible patient list. For six different purposively selected practices, randomization is performed automatically by using a simple randomization procedure programmed into the information system that is used to manage the Health Check Program (automated method). For the automated method, simple randomization, stratified by practice, is being used. A randomization program has been written, and participants are automatically assigned a study ID and group allocation when the clean lists are electronically approved. Each practice is participating in the trial for a minimum of 12 months to allow seasonal variation in uptake of Health Checks.

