### Sample size

It will be important to detect even modest increments in screening uptake between trial arms, because in a public health program, small effects may yield substantial benefits across the population at risk. We make the statistically conservative assumption that the underlying proportion of people invited who actually receive a Health Check is about 50%. With 4,263 participants in each trial arm, with 12,789 in total, this provides more than 90% power to detect a difference in uptake of Health Checks between each active treatment arm and the standard intervention arm of at least 4%. These calculations are based on 5% significance level by using a Bonferroni correction for three comparisons. The calculations were performed in Stata version 12 [26]. Because present rates of Health Check uptake are below 50% in the study area, slightly greater power may be realized in the study. No planned interim analysis and no stopping guidelines exist, as this trial has a low risk of adverse events.

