### Statistical methods

The analysis will be on an intention-to-treat basis and will include all patients who are randomized, regardless of subsequent actions (for example, if the questionnaire was not sent out, participants will still be analyzed in the group to which they were randomized). For participants who die or leave their general practice within 6 months of the standard invitation, we will use the Health Check uptake status at the end of registration as their outcome.

In an individually randomized trial, Health Check uptake may vary between general practices, as, for example, if a practice nurse follows-up patients for an appointment. We will quantify the extent of between-practice variation by tabulating the outcome by general practice and estimating an intraclass correlation coefficient by using analysis of variance.

To adjust for practice-effect in the primary analysis, we will fit a marginal model by using the method of generalized estimating equations (GEEs), allowing for clustering by practice by using an exchangeable correlation structure and model-based variance estimates, as the number of practices is relatively small [27]. Covariates will be age, gender, month of invitation, deprivation quintile, and arm comparing outcomes between arms A versus B, A versus C, and B versus C, with adjustment for multiple comparisons.

The GEE model will be implemented by using the binomial family and an identity link to estimate the adjusted risk difference. Because we are primarily interested in absolute differences in NHS Health Check uptake, rather than in relative measures such as odds ratios, we will implement covariate adjustment by the method of inverse probability weighting by using the propensity score as suggested by Ukoumunne *et al*. [28]. Interaction terms will be tested, and, where appropriate, intervention effects will be estimated by subgroup. The slope index of inequality (SII) [29] will be used as a metric to estimate the difference in screening uptake between the least- and the most-deprived quintiles (local IMD scores will be classified into quintiles of the distribution of IMD scores in England for reference), and we will test whether SII differs between trial arms.

All estimates will be presented with 95% confidence intervals and *P* values. The trial will be reported according to CONSORT recommendations.

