Secondary analyses to examine whether outcomes and intervention effects vary by deprivation quintile, gender, or age-group will be performed in a similar manner as stated earlier and will include exploring interaction effects. The delay in uptake between arms will be examined by using time-to-event analysis. The duration between the date the invitation was sent and the booked appointment will be calculated. Differences will initially be visually assessed by using Kaplan-Meier curves, and then an appropriate time-to-event model with robust variance estimates allowing clustering by practice will be fitted, adjusting for age, gender, month, and deprivation quintile.

To evaluate the consistency of estimates obtained by using the two different randomization methods, subgroup analyses will be performed for each randomization method separately. A meta-analysis will be performed, by using each participating general practice as the unit of analysis, with results pooled for each randomization method separately and across all practices. A test for heterogeneity will be performed.

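### The time-to-event model relies on robust variance clustered on 18 practices with no stated small-sample correction, so nominal 95% intervals for the timing outcome cover about 92-93%

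*Protocol article*

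**What the plan says.** The Outcomes section lists time from standard invitation to Health Check as a secondary outcome. For its analysis, the Secondary analyses section states that, after Kaplan-Meier curves, "an appropriate time-to-event model with robust variance estimates allowing clustering by practice will be fitted", with adjustment for age, gender, month and deprivation quintile. It does not name the model, a finite-sample factor or a reference distribution.

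For the primary analysis, the Statistical methods section fits a GEE with an exchangeable correlation by practice and "model-based variance estimates, as the number of practices is relatively small". That section also promises 95% confidence intervals and P values for all estimates.

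The number of practices comes from Recruitment and randomization: "For 12 purposively selected practices (from those who consent), researchers visit each practice monthly" and "For six different purposively selected practices, randomization is performed automatically". Individuals are randomized, with allocation stratified by practice.

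**The concern.** A practice-clustered sandwich variance is built from one score contribution per practice. With 18 contributions it tends to be too small and is itself imprecise. A test statistic based on it behaves roughly like a t variable with 17 degrees of freedom, not like a normal one. Using 1.96 as the critical value then gives intervals that are too narrow and P values that are too small.

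The plan shows that it knows the number of practices is small, because it gives this as its reason for the variance used in the primary model. The reason concerns the number of clusters, not the type of outcome, so it carries over to the time-to-event model on the same practices. The plan neither takes it up there nor explains why a different estimator is used. At stake are the interval and P value for one secondary outcome.

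**Working it through.** **Inputs from the protocol article.** Practices: 12 + 6 = 18 (Recruitment and randomization). Sample size: "With 4,263 participants in each trial arm, with 12,789 in total" (Sample size), so 12,789/18 = about 710 patients per practice, or about 474 in any two arms. Uptake: 32% and 38% in the two boroughs (Setting and participants), taken as 35% by 182 days. Nominal level: 5% two-sided, from the 95% intervals.

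**Assumptions not in the article.** Cox form, constant hazard, no covariates, two arms compared, gamma practice frailty with variance 0, 0.1 or 0.3, and practice sizes either equal or lognormal with SD 0.6.

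**Step 1: the plan's own figure.** The article gives no error rate for this model. Its sample size can be reproduced. For 50% versus 54%, 90% power and two-sided alpha 0.05/3 = 0.0167 ("These calculations are based on 5% significance level by using a Bonferroni correction for three comparisons"), the two-proportion formula gives 4,213 per arm, or 4,263 with continuity correction. The latter is the stated number.

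**Step 2: approximation.** With G = 18 and a normal critical value of 1.96:
- Uncorrected sandwich: 2 × P(t17 > 1.96 × √(17/18)) = 2 × P(t17 > 1.905) = 7.4%.
- With the G/(G-1) factor: 2 × P(t17 > 1.96) = 6.7%.

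**Step 3: null simulation.** Individuals were allocated within practice, with N = 12,789 and 6,000 replicates per row (Monte Carlo standard error about 0.3 points). Entries are rejection rates at nominal 5% for an unstratified Cox model.

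| Practice sizes | Frailty variance | Robust, normal | Robust × G/(G-1), normal | Robust × G/(G-1), t17 | Model-based |
|---|---|---|---|---|---|
| Equal | 0 | 7.8% | 6.9% | 5.4% | 4.9% |
| Equal | 0.1 | 7.3% | 6.7% | 4.8% | 4.2% |
| Equal | 0.3 | 7.8% | 6.9% | 4.9% | 3.8% |
| Unequal | 0 | 7.7% | 6.9% | 5.3% | 4.4% |
| Unequal | 0.1 | 8.4% | 7.5% | 5.9% | 4.8% |
| Unequal | 0.3 | 7.9% | 7.3% | 5.9% | 4.0% |

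Restricting to attenders (unequal sizes, frailty variance 0.1) gives 7.9% uncorrected and 7.1% with the factor. The rates barely move with the frailty variance, as expected if the number of clusters is the cause. Coverage is 100% minus the rejection rate: 91.6% to 92.7% uncorrected and 92.5% to 93.3% with the factor, so about 92-93%.

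**Step 4: the two remedies under the null of no effect in any practice.** Robust variance with G/(G-1) and t on 17 degrees of freedom rejects 4.8%-5.9% (table). A Cox model stratified by practice with model-based variance, simulated separately, rejects 4.5%-5.3%.

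**Step 5: the remedies if the arm effect varies between practices.** With 474 × 0.35 = about 166 events per practice, the within-practice variance of the log hazard ratio is about v = 4/166 = 0.024. If the true effect varies with SD τ around an average of zero, the stratified model-based test rejects with probability 2 × P(Z > 1.96/√(1 + τ²/v)). This gives 5.0% at τ = 0, 6.2% at 0.05 and 9.9% at 0.10. A simulation at τ = 0.08 gave 7.7% for the stratified model and 4.8% for the corrected robust variance. These values of τ are assumptions.

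**The case against.** The strongest reply is that the two choices need not conflict. In a GEE with an exchangeable working correlation, the model-based variance already carries the clustering. An ordinary marginal survival model has no such term, and a robust variance is the usual way to bring practice in. The Statistical methods section never mentions robust variance. A reader might infer that the plan rejects it and then contradicts itself, but the text does not go that far. This part of the objection stands. What remains is that the same few practices are recognised as a problem in one model and left unaddressed in the other.

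A second reply is that the article leaves open the model, the finite-sample factor and the reference distribution, so an analysis plan could add a correction without departing from it. That is true, and it is why the size depends on implementation. It does not dispose of the point, because the article does fix the estimator, and that estimator with the usual normal reference under-covers.

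A third reply is that practice-clustered robust variance is not superfluous merely because patients are randomized within practice. It also reflects variation of the arm effect between practices, which the plan means to examine through a practice-level meta-analysis with a heterogeneity test. This stands too, and it is why the remedy keeps the robust variance.

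Two further readings are tempting but unsupported. One is that the error roughly doubles at a Bonferroni level of 1.67%: no multiplicity adjustment is stated for the time-to-event model. The other is that error rates reach 8.2%-10.1% with 12 practices and 12.5%-15.4% with six: the article does not say that this model will be fitted separately by randomization method.

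**Conclusion.** The point holds as a modest defect in one secondary analysis. As specified, and with the usual normal reference, the false-positive rate is about 7-8% at nominal 5%, or about 7% if the software applies G/(G-1). The figure rests on a Cox model without covariates and on assumed practice heterogeneity and sizes, but it changed little over the range tried and agrees with the t approximation. It should not be read as a fault in the primary GEE or the sample size, neither of which depends on this variance. Nor is there evidence that the correction would alter a conclusion about timing.

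**What to change.** Before the outcome data are analysed, add to the time-to-event paragraph that the practice-clustered robust variance will carry a small-sample correction, at least the factor G/(G-1), and that tests and intervals will use a t distribution on 17 degrees of freedom. The t critical value is 2.11 against 1.96, so intervals widen by 2.11/1.96 = 1.08. They widen by 1.08 × √(18/17) = 1.11 if the software was not already applying the factor. The cost is therefore intervals about 8-11% wider and one sentence of text.

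The alternative is to stratify the model by practice, the randomization stratum, with a separate baseline hazard for each practice and model-based variance. If this is chosen, the plan should say that the test concerns no effect in any practice and that the standard error does not reflect variation of the arm effect between practices. Whichever is chosen, a short reason for using a different variance estimator from the primary GEE would settle the discrepancy.

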### Economic evaluation

If either the enhanced invitation or the enhance invitation with incentives arms are more effective in increasing uptake than standard practice, we will analyze the cost-effectiveness of these treatments. The additional costs to the health service of an enhanced invitation and financial incentives will be estimated. Although these programs would add costs, they will be assessed against the potential long-term health benefits of NHS Health Checks by using existing models to estimate the cost-effectiveness of the Health Check program developed both nationally [6] and locally.

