**Method:**

The project is a three-arm randomized controlled trial to test the hypothesis that enhanced invitation methods, using the Question-Behaviour Effect (QBE), will increase uptake of NHS Health Checks compared with a standard invitation. Participants comprise individuals eligible for an NHS Health Check registered in two London boroughs. Participants are randomized into one of three arms. Group A receives the standard NHS Health Check invitation letter, information sheet, and reminder letter at 12 weeks for nonattenders. Group B receives a QBE questionnaire 1 week before receiving the standard invitation, information sheet, and reminder letter where appropriate. Group C is the same as Group B, but participants are offered a £5 retail voucher if they return the questionnaire. Participants are randomized in equal proportions, stratified by general practice. The primary outcome is uptake of NHS Health Checks 6 months after invitation from electronic health records. We will estimate the incremental health service cost per additional completed Health Check for trial groups B and C versus trial arm A, as well as evaluating the impact of the QBE questionnaire, and questionnaire plus voucher, on the socioeconomic inequality in uptake of Health Checks.

The trial includes a nested comparison of two methods for implementing allocation, one implemented manually at general practices and the other implemented automatically through the information systems used to generate invitations for the Health Check.

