### Objectives

The aim of this research is to determine whether enhanced invitation methods, in using the QBE, lead to increased uptake of NHS Health Checks. The specific objectives of this research are as follows:To implement a randomized controlled trial (RCT) with individual participants who are eligible for NHS Health Checks as the unit of allocation. The trial will compare the effects of: standard invitation only; QBE questionnaire followed by standard invitation 1 week later; QBE questionnaire, with offer of retail voucher as incentive for questionnaire completion, followed by standard invitation 1 week later. The intervention effect will be evaluated by using the primary outcome of whether each individual completed the NHS Health Check within 182 days (6 months) of the standard invitation being sent.To estimate the incremental health service cost per additional health check completed for the QBE questionnaire, and the QBE questionnaire-plus-voucher trial arms, in comparison with the standard invitation.To evaluate the impact of the QBE questionnaire, and the QBE questionnaire plus voucher, on inequality in uptake of Health Checks between most- and least-deprived areas of residence based on the Indices of Multiple Deprivation (IMD 2010) score by postcode of residence.

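### The cost-effectiveness analysis hangs on an undefined effectiveness condition that Objective 2 does not contain, and no economic comparison of the voucher arm with the questionnaire-only arm is planned

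*Protocol article*

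**What the plan says.** Three places in the protocol article bear on the economic analysis.

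- **Abstract, Method:** "We will estimate the incremental health service cost per additional completed Health Check for trial groups B and C versus trial arm A". There is no condition, and the comparator is arm A.
- **Objectives, second objective:** "To estimate the incremental health service cost per additional health check completed for the QBE questionnaire" and for the "QBE questionnaire-plus-voucher trial arms, in comparison with the standard invitation". Again there is no condition, and the only comparator is the standard invitation.
- **Economic evaluation:** the first sentence begins "If either the enhanced invitation or the enhance invitation with incentives arms are more effective in increasing uptake than standard practice" and continues "we will analyze the cost-effectiveness of these treatments". The second sentence carries no condition: "The additional costs to the health service of an enhanced invitation and financial incentives will be estimated". The third says that these costs will be set against long-term health benefits, using existing models of the programme. The section does not mention cost per additional check and gives no criterion for effectiveness.

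Two other sections matter. Interventions describes arm C as the arm B mailing with a covering letter that offers a £5 voucher for returning the questionnaire. Statistical methods plans the uptake analysis with "arm comparing outcomes between arms A versus B, A versus C, and B versus C, with adjustment for multiple comparisons".

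**The concern.** There are two separate issues.

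**The condition.** An objective stated without qualification meets a Methods section whose opening sentence is conditional on the primary result. The condition could mean a higher point estimate, nominal significance, or significance after the multiplicity correction, and these lead to very different chances that the analysis is done. If the condition covers everything in the section, a null result would leave Objective 2 unanswered. That would sit badly with the Sample size section, which argues that small effects matter in a public health programme.

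**The comparator.** Arms A, B and C are successive steps: nothing added, a questionnaire, and a questionnaire plus a voucher. A service that could adopt B needs to know what the voucher buys beyond B. The ratio of C to A blends the first step with the second, so a voucher that adds little can look acceptable because the questionnaire has carried it. The Discussion foresees roll-out across the NHS, so the choice between B and C is a real decision.

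**Working it through.** **1. The plan's own figure.** The economic section states no number. The only figure needed is the sample size, because it fixes how often a significance condition would be met. Inputs from Sample size: 50% versus 54%, 90% power, 5% level with Bonferroni correction for three comparisons (0.05/3 = 0.0167, taken as two-sided).

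n = [z(α/2)·√(2p̄(1−p̄)) + z(β)·√(p₁(1−p₁) + p₂(1−p₂))]² / (p₂−p₁)²

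= [2.394·√0.4992 + 1.2816·√0.4984]² / 0.04² = 4,213 per arm, or 4,263 with continuity correction. This is the stated figure exactly. The sample size is not in question.

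**2. How much the undefined term matters.** Suppose the true gain is 2 points in both B and C, with control uptake 50% and 4,263 per arm. The standard error of each difference is √[(0.50·0.50 + 0.52·0.48)/4,263] = 0.0108. The chance that the condition is met is then:

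| Reading of the condition | Chance met |
|---|---|
| A given arm significant at 0.0167 | 29% |
| Either arm significant at 0.0167 (shared control, correlation 0.5) | 43% |
| Either arm has a higher point estimate than A | 99% |

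On the arm-by-arm significance reading, the chance for true gains of 1, 2, 3 and 4 points is 7%, 29%, 65% and 90%.

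**3. Ratios against A and between C and B.** Let c be the extra cost per person invited and d the gain in uptake over A. Then B versus A = c_B/d_B, C versus A = c_C/d_C, and C versus B = (c_C − c_B)/(d_C − d_B). Only the £5 comes from the protocol; mailing cost, proportion claiming and gains are assumptions.

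*Base illustration:* mailing £1.50, 30% of arm C claim the voucher (0.30 × £5 = £1.50), gains of 3 and 4 points.
- B versus A: 1.50/0.03 = £50
- C versus A: 3.00/0.04 = £75
- C versus B: 1.50/0.01 = £150

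The middle figure is a weighted average of the two steps: (3/4)·50 + (1/4)·150 = £75.

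*Range:*

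| Mailing | Claim | Gain B, C (points) | B v A | C v A | C v B |
|---|---|---|---|---|---|
| £1.50 | 30% | 3, 3.5 | £50 | £86 | £300 |
| £1.50 | 30% | 3, 3 | £50 | £100 | B dominates |
| £1 | 35% | 3, 3.5 | £33 | £79 | £350 |
| £1 | 35% | 2, 4 | £50 | £69 | £87.50 |
| £2 | 35% | 2, 4 | £100 | £94 | £87.50 |

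The contrast can be large, small or reversed. In the dominated case, C versus A is still an ordinary-looking number.

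**The case against.** **The condition may be narrower than it looks.** Cost per completed check and cost-effectiveness judged against long-term health benefit are different analyses. The costing sentence has no condition. A coherent reading is that costs and cost per check are always estimated and only the modelling waits on the uptake result. This stands as a possible reading, so a flat contradiction is not proved. But the section never says that it governs only the modelling and never mentions cost per additional check, so the reading has to be supplied by the reader.

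**C versus B can be worked out anyway.** Uptake is compared between B and C, the costs of the invitation and of the incentives are to be estimated, and questionnaire response is analysed by group. This also stands: a reader might infer that the trial cannot say whether the voucher is worth its cost, and the document does not support that. What remains is that the ratio is not among the planned results.

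**Bias from the condition.** A reader might also infer that the condition makes the cost per check look too low. With a true gain of 2 points and an arm-by-arm significance rule, the mean estimate among trials that pass is 3.27 points, and 2/3.27 = 0.61 suggests a 39% understatement. The document does not support that as a finding. No significance rule is stated. The effect is also one of selection across hypothetical repeats: a trial that passes reports the same ratio whether or not the condition exists.

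**An article condenses.** Resampling details and the like may be left to a fuller plan. The trigger and the comparators, however, are stated here, and the point concerns what is stated.

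**Conclusion.** The point holds in a limited form. The Economic evaluation section imposes an undefined condition that the abstract and Objective 2 lack, and the text does not settle whether it covers the cost per additional check. If it does, Objective 2 goes unreported after a null result. How likely that is depends on the unstated criterion: at a true 2-point gain in both arms, the condition would be met anywhere from 29% to 99% of the time across the readings above.

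The economic comparisons named are both against A, and the one that isolates the voucher is not planned. The size of this gap cannot be fixed from the document. On the base assumptions, £75 against A stands in place of £150 against B, but other plausible inputs narrow or reverse the contrast. The firm part needs no cost assumption beyond the voucher adding cost: if C costs more than B and gains no more uptake, B dominates it, yet C versus A stays finite so long as C beats A. The primary uptake analysis and the sample size are unaffected.

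**What to change.** 1. State in Economic evaluation that costs, uptake differences and cost per additional completed check, with their uncertainty, will be reported for all three arms whatever the primary result.
2. If a condition is wanted, confine it to the long-term modelling and define it: which arm, which estimate or test, and at what level.
3. Replace the pair of ratios against A with a full incremental analysis: order the arms by cost, report B versus A and C versus B, apply dominance, and keep C versus A as a supplement. Align the abstract and Objective 2 with this.

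The cost is wording and a little extra analysis on data already to be collected. No change to recruitment, sample size or follow-up is needed, and with recruitment still under way the change can be made before results are known.
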